
## 1. Background

Preoperative anxiety and stress are a frequently encountered phenomenon among patients, while such anxiety is experienced on different levels based on sociodemographic characteristics. The overall prevalence of preoperative anxiety varies and is reported in a range of 60–80% while other studies showed a wider range of 11–80% [1,2,3,4,5]. It occurs as a compatible and physiological response to surgical encounters and stress, which might occur anytime preoperatively [6]. The anxiety and stress are induced during hospitalization and intensified when a patient is informed about the need to undergo surgical intervention, and shortly before surgery [7].

Preoperative stress-related signs are associated with a potential change in patients’ psychological responses and hemodynamic parameters, including increased blood pressure and heart rate, that may pose a danger to the patients’ health [8]. Thus, these changes might affect the quality of anesthesia and demand for analgesics, postoperative pain, and possible delirium [9].

It also has significant impact on recovery, including longer postoperative hospital stay and even cognitive and behavioral ramifications. Thus, procedures which are painful lead to preoperative and postoperative anxiety, which causes fear in patients. This leads to a reduced pain threshold and higher postoperative pain and can affect patients’ compliance with subsequent future procedures [10]. A meta-analysis revealed that social support is crucial in reducing the postoperative anxiety among patients undergoing elective surgery. Conventional methods and interventions for managing pain and anxiety typically involve patient education and therapy with anti-anxiety medications prior to surgery to enhance patients’ comfort. However, randomized controlled trials have reported that these approaches provide only limited effectiveness and are associated with risks such as side effects, dependence, drug tolerance, and prolonged recovery time. As a result, there is increasing demand for non-pharmacological interventions to manage pain and anxiety, mitigating the drawbacks and risks associated with this traditional approach [11,12].

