## 2. Pathomechanism of Pain and Anxiety

There is a strong correlation between anxiety and pain. To comprehend the mechanistic beginnings for VR analgesia, the neurobiological connectivity of the brain’s cortices and neurochemistry have been investigated, including the attentional, emotional, and cognitive processes [26].

Various receptors and proteins have been revealed to mediate pain attributed to periphery, as well as at the spinal cord level, where the gate control of pain transmission is located [27].

Nonetheless, anxiety has been researched mainly within the context of neuropsychology. Recent research on neuroimaging has revealed the brain’s inner network and how it mediates interactions of pain and anxiety. Both healthy participants and patients with emotional symptoms had key cortical areas actively involved in both conditions, including the anterior cingulate cortex (ACC), insular cortex (IC), and amygdala. Moreover, integrative neurobiological tools have allowed the central synapses to be investigated, as well as their potential involvement in anxiety disorders and chronic pain [27,28,29,30,31].

The human brain’s response to painful stimuli has been captured in functional imaging studies, with activity in the insula, anterior cingulate gyrus, the thalamus, and the primary somatosensory cortex and the periaqueductal gray matter. These regions host a network of circuitry that is involved from the top-down, bottom-up, and intercortical processing of such painful stimuli, and are the origins of where pain is perceived.

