### 4.3. Participant Sample and Sample Size

#### 4.3.1. Recruitment and Allocation

The sample size calculation is based on detecting a clinically meaningful reduction in preoperative anxiety measured by the State-Trait Anxiety Inventory–State (STAI-S) score, which is the primary endpoint. The trial was powered based on the primary endpoint of STAI-S change. Prior VR perioperative studies report a mean reduction of 8–10 points with a standard deviation of approximately 10 points. Using Rosner’s formula for three parallel study arms, with α = 0.05, power = 0.80, and a minimum clinically significant difference of 8 points, 42 patients per arm are required. To account for an anticipated 15% attrition rate, we will enroll 50 participants per arm, for a total sample size of 150 patients. Elective procedures are defined as those happening the day after the initial patient evaluation. All patients will be provided with written informed consent, and the trial procedures will be explained verbally and in writing to all patients prior to study enrolment.

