### 4.8. Data Collection

#### Baseline Value Measurement

On the day before surgery, after informed consent is obtained, evaluations, which include sociodemographic data and the psychometric questionnaires (STAI-S, PSS-10, BDI-II), pain score (VAS), and satisfaction (EVAN-G), will be collected by the researcher before the VR experience (see Table 3).

Perioperative anesthesia and analgesia management will follow standardized institutional protocols whenever feasible. Variables including anesthetic technique, intraoperative opioid administration, postoperative opioid consumption, rescue analgesic use, surgery duration, and perioperative complications will be prospectively recorded and considered in adjusted secondary analyses.

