### 4.9. Statistical Analysis

The statistical analysis will be performed under the mentorship of a biostatistician experienced in neurosurgical research. The nominal data will be presented as *n* (% of the total). The dependencies between them will be assessed using the test chosen based on the size of the smallest sample. All analyses will follow an intention-to-treat approach. The primary endpoint (change in STAI-S score from baseline to immediately postintervention) will be analyzed using one-way ANCOVA adjusted for baseline STAI-S. Pairwise comparisons will be Bonferroni-corrected. Secondary outcomes will be analyzed as follows: VAS pain at 24 h (ANCOVA adjusted for opioid dose), total opioid consumption (ANOVA or Kruskal–Wallis depending on distribution), patient satisfaction (Kruskal–Wallis), and rescue analgesic use (χ^2^ test). Longitudinal measures (baseline → post-VR → postoperative) will be evaluated with a linear mixed-effects model including group, time, and group × time interaction. Normality will be tested using the Shapiro–Wilk test. Missing data will be assessed for pattern and mechanism. Multiple imputation (m = 10) will be used if appropriate. Longitudinal analyses will primarily rely on linear mixed-effects models, which are robust to missing observations under missing-at-random assumptions. The primary comparison will evaluate procedural/educational VR versus standard care with respect to STAI-S score change. Secondary comparisons will include relaxation/distraction VR versus standard care and procedural/educational VR versus relaxation/distraction VR. Postoperative pain analyses will additionally be adjusted for perioperative opioid consumption and surgery duration when appropriate. Statistical analysis will be performed using STATISTICA 13.1 (TIBCO, Palo Alto, Santa Clara, CA, USA) and two-sided α = 0.05.

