## Figures and Tables

**Table 1 brainsci-16-00587-t001:** Eligibility Criteria for Study Enrollment.

Inclusion Criteria	Exclusion Criteria
Adult patients between 18–70 years old Patient’s admission prior to surgery day (at least 1 day) Patients’ first surgery with no prior surgical history cervical vs. lumbar vs. thoracic) Type of spine surgery (e.g., cervical vs. lumbar vs. thoracic) Surgical approach (e.g., minimally invasive vs. open) Anesthetic technique (e.g., general) Expected hospital stay—2 days Capable of providing informed consent and participate in the study follow-up questionnaire Patients speak English	Congestive heart failure, hypertension and anti-hypertensive medications Adrenal insufficiency Cognitive impairment (evaluated by MMSE, MoCA) Cerebrovascular diseases, ophthalmological diseases (strabismus, diplopia, retina degeneration, glaucoma), neurological conditions (epilepsy or seizure, dementia, vertigo, dizziness, motion sickness)—evaluated by: history taking, examination, vision test (Ishihara test) Auditory impairment Psychiatric illness (schizophrenia, bipolar disorder, psychotic depression)—(evaluated by MINI questionnaire) Patients with neuropathic pain Use of sedative drugs, anti-depressants, anxiolytics, and anti-epileptic drugs Claustrophobia GCS < 15

**Legend:** MMSE, Mini-Mental State Examination; MoCA, Montreal Cognitive Assessment; MINI, The Mini International Neuropsychiatric Interview; GCS, Glasgow Coma Scale.

**Table 2 brainsci-16-00587-t002:** Primary and secondary outcome assessment.

Timepoint	Assessment	Measures
Day before surgery (pre-VR)	Baseline	STAI-S, VAS pain
Day before surgery (post-VR)	Immediately after VR intervention	STAI-S, VAS pain, patient experience satisfaction
Within 24 h after surgery	Postoperative	VAS pain, analgesic use

**Table 3 brainsci-16-00587-t003:** Preoperative and postoperative psychometric scales.

Baseline Values
Patients’ demographics: age, sex, education, medical history (comorbidities), medication, surgery type, duration, ASA status Anxiety (STAI-S) Stress (PSS-10) Depression (BDI-II) Pain score (VAS) Satisfaction (EVAN-G) Cognitive (ACE-III) Personality test (PID-5) Postoperative analgesia (Medical charts and records)

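### Baseline STAI-S is collected from every patient and the protocol ties anxiety to postoperative pain, yet the 24 h pain and opioid analyses do not adjust for it: a modest loss of precision, not a bias

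*Protocol article*

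**What the plan says.** **What is collected.** The Baseline Value Measurement text in section 4.8 lists "the psychometric questionnaires (STAI-S, PSS-10, BDI-II), pain score (VAS") among the assessments made before the VR experience, and Table 3 repeats the scales. The timeline in section 4.5 puts these assessments before randomisation.

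**What is analysed.** Section 4.9 names the method for each outcome:
- STAI-S change (primary): ANCOVA with baseline STAI-S as covariate.
- Pain and opioid use: "VAS pain at 24 h (ANCOVA adjusted for opioid dose), total opioid consumption", the latter by ANOVA or Kruskal–Wallis according to distribution. Pain analyses may also take perioperative opioid consumption and surgery duration.
- Satisfaction: Kruskal–Wallis. Rescue analgesic use: chi-square.
- Longitudinal measures: a mixed model with group, time and their interaction.

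The variables that sections 4.1 and 4.8 name for adjusted analyses are surgical, anaesthetic and analgesic. No psychometric score is among them.

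**What the protocol believes about anxiety and pain.** Of anxiety and the fear that it causes, the Background says: "This leads to a reduced pain threshold and higher postoperative pain". Section 2 opens with: "There is a strong correlation between anxiety and pain". The Discussion also links anxiety to increased pain, through sympathetic activity. On analgesic demand the Background is more cautious: it says only that stress-related changes might affect it.

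**The concern.** The trial rests on a pathway from preoperative anxiety to postoperative pain, and it holds a pre-intervention anxiety score for every patient. That score is used for the anxiety endpoint and then left out of the model for pain, the outcome that the protocol says anxiety influences.

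Two things are at stake. First, if baseline STAI-S predicts 24 h pain, the confidence intervals for the arm differences are wider than they need be. Second, section 4.4 describes permuted blocks of six and mentions no stratification by anxiety, so anxious patients are balanced across arms only by chance. An unadjusted comparison carries any imbalance into the pain difference, where it could pass for a VR effect or mask one.

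The article does not simply leave this to a fuller document. It sets the models outcome by outcome and names their covariates, so the question is whether what it fixes is fixed well.

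**Working it through.** **Inputs from section 4.3.1.** The article plans "To account for an anticipated 15% attrition rate, we will enroll 50 participants per arm, for a total sample size of 150 patients". The attrition step reproduces: 42 / 0.85 = 49.4, rounded up to 50. I take 42 evaluable per arm, 126 in all, and the two-sided α = 0.05 of section 4.9.

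The figure of 42 itself does not follow from its stated inputs (difference 8, SD about 10, power 0.80): 2 × (1.96 + 0.84)² × 10² / 8² = 24.5, so 25 per arm, or 33 at α = 0.05/3. That is a separate matter. It concerns the primary endpoint and does not affect what follows.

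**Inputs not in the documents.** There is no correlation between baseline STAI-S and 24 h pain or opioid use, and no effect size, SD or power for any secondary outcome. I therefore assume r from 0.1 to 0.4, read as a partial correlation given the other terms in the model. As a reference I take a comparison that would have 80% power without the covariate.

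**Precision.**
- Residual variance factor: 1 − r².
- Equivalent patients per arm: 42 / (1 − r²).
- Power: Φ(2.80 / √(1 − r²) − 1.96).
- Variance ratio after paying for one estimated covariate in three arms: (1 − r²) × (1 + 1/(126 − 3 − 1 − 2)) = (1 − r²) × 1.0083.

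| Assumed r | Variance reduction | Equivalent n per arm | Power from 80% | Variance ratio after cost |
|---|---|---|---|---|
| 0.1 | 1% | 42.4 | 80.4% | 0.998 |
| 0.2 | 4% | 43.8 | 81.6% | 0.968 |
| 0.3 | 9% | 46.2 | 83.6% | 0.918 |
| 0.4 | 16% | 50.0 | 86.4% | 0.847 |

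At r = 0.1 the gain is 0.2% of variance, which is nothing in practice. With three covariates (STAI-S, PSS-10 and BDI-II) the cost factor is 1 + 3/118 = 1.025. A multiple correlation of 0.1 then gives 0.99 × 1.025 = 1.015, a small net loss.

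**Chance imbalance.** The SD of the difference in mean baseline STAI-S between two arms of 42 is √(2/42) = 0.218 SD. The imbalance exceeded in either direction in 1 trial in 20 is 1.96 × 0.218 = 0.43 SD. It shifts the unadjusted outcome difference by r × 0.43 SD, that is 0.09 to 0.17 SD for r = 0.2 to 0.4.

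Given exactly that imbalance and no true effect, the test statistic has mean 1.96r and variance 1 − r². The chance that it exceeds 1.96 in absolute value is then 6.3%, 7.9% and 10.1% for r = 0.2, 0.3 and 0.4. These are conditional rates. Averaged over all randomisations the rate is 5%.

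**The case against.** The strongest reply is that nothing here is wrong. A randomised comparison without a prognostic covariate is valid, and the same calculation could be made for any covariate left out of any trial. That stands, and it limits the point to efficiency. A reader might infer from the conditional 6% to 10% that the planned tests are biased or exceed their level. They do not, because the nominal 5% already averages over good and bad imbalances.

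A reader might also infer that the protocol presents depression as a cause of pain or analgesic demand, or a baseline score as a predictor of satisfaction, so that all three scores belong in every secondary model. The documents do not support this. No passage links depression to either outcome, none ties a baseline psychometric score to satisfaction, and the statement on analgesic demand is hedged. The rationale is firm only for anxiety and pain.

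The size of the gain is also fairly questioned. It rests on an assumed r. Table 1 excludes users of sedatives, antidepressants and anxiolytics, which may narrow the range of STAI-S and lower r. Baseline VAS, if added, could take up part of the gain.

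Replacing rank tests by linear models for skewed opioid totals or satisfaction scores could lose as much as the covariate gains, so the rank tests should stay.

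Further covariates for secondary outcomes are often left to a statistical analysis plan, and the list in section 4.8 is not closed. But section 4.9 does name the covariate for the 24 h pain ANCOVA, and baseline STAI-S is not it.

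Finally, the covariate that it does name, opioid dose, arises after randomisation and is itself close to an outcome. That is a weightier, separate problem, and adding STAI-S does not cure it.

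**Conclusion.** The point holds as a missed efficiency, confined to baseline STAI-S in the 24 h pain analysis and in the opioid analysis where a parametric model is used. For assumed r between 0.2 and 0.4 the gain is 4% to 16% of residual variance, or about 2 to 6 power points from a hypothetical 80%. At r near 0.1 it is essentially nil. Adjustment would also remove the effect of a chance imbalance in baseline anxiety, which the planned models leave in. The primary endpoint is unaffected, since its ANCOVA already uses baseline STAI-S. The case is stronger for pain than for opioid use, because the protocol asserts the link to pain and only allows for one to analgesic demand.

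**What to change.** In section 4.9, pre-specify before unblinding:
- Baseline STAI-S enters the 24 h VAS pain ANCOVA as a fixed covariate, whatever the observed balance between arms.
- Where total opioid consumption is analysed parametrically, ANCOVA with baseline STAI-S replaces one-way ANOVA.
- Rank-based tests remain for skewed opioid totals and for satisfaction, without covariates.

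BDI-II and PSS-10 are optional. If they are wanted, they should be named now and not chosen after seeing the data.

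The cost is a sentence or two of text and one degree of freedom per model, with no new data and no extra patients.

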## 3. Objectives

The aim of this research study is to evaluate the impact of immersive VR exposure on preoperative anxiety and pain, and, additionally, to assess whether VR intervention would significantly alleviate pain and anxiety levels of patients undergoing complex spinal surgeries. We hypothesize that the application of preoperative VR-based intervention will alleviate anxiety and pain both pre- and postoperatively when it is used as treatment to complement standard care compared to standard routine care alone, and that it may lead to better outcomes and higher satisfaction in patients. The primary objective is to evaluate whether procedural/educational VR reduces preoperative anxiety compared with standard care. Secondary objectives include comparing relaxation/distraction VR versus standard care, and procedural/educational VR versus relaxation/distraction VR with respect to postoperative pain, analgesic use, and patient satisfaction.

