### 4.5. Instruments and VR Utilization

The study affects all three groups, and the VR intervention includes only one session. All intervention sessions will be carried out individually. After these assessments, the patients will be oriented to the VR goggles and headset and given tutorials and instructions on how to use the device and how to remove it when they encounter potentially unwanted side effects such as dizziness, headache, nausea, or vomiting. In such cases, the procedure will be stopped and considered a withdrawal.

On the day before surgery, following baseline assessment and informed consent, the researcher will randomly allocate the patients to the VR group, control group, and VR relaxation/distraction group.

The study timeline will proceed as follows: enrollment and informed consent → baseline psychometric and pain assessments → randomization → VR or standard-care intervention on the day before surgery → immediate postintervention assessment → surgery → postoperative assessment within 24 h and analgesic assessment within 24–48 h postoperatively.

VR-related adverse effects, including dizziness, nausea, headache, cybersickness, and visual discomfort, will be prospectively recorded and analyzed descriptively throughout the intervention period.

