#### 4.7.4. Clinical Outcome Variables and Assessment

The primary outcome is the change in STAI-S score from baseline to immediately after intervention. Secondary outcomes include postoperative pain intensity assessed using the Visual Analogue Scale (VAS), postoperative analgesic use, patient satisfaction, and VR-related adverse effects. These outcomes will be measured preoperatively on the day before surgery, before the VR content exposure, and after. Measurements will be made again postoperatively—within 24 h. Preoperative and postoperative STAI-S and VAS will be compared for data analysis.

The baseline assessment is conducted one day before surgery, prior to the VR intervention, to capture the patient’s preoperative state under conditions closest to the actual surgical context. We believe this timing best reflects the anxiety and pain levels that the VR intervention aims to reduce. The postoperative assessment within 24 h is intended to evaluate the immediate effect of the intervention on perioperative anxiety and pain, which is the primary focus of our study. We acknowledge that longer-term outcomes may differ, but these are beyond the scope of the current trial, which specifically targets the short-term perioperative period (see Table 2).

The secondary outcome will be the patients’ quality of life and satisfaction (EVAN-G) of the VR intervention, time spent thinking about pain assessed, and postoperative analgesics measured from patient treatment charts within 24 and 48 h postoperatively and used for data analysis, as the level of satisfaction and thinking time spent on pain can contribute to an increased perception of pain.

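### The 24 h pain ANCOVA adjusts for opioid dose, a post-randomisation outcome, so its arm difference can misstate the effect of VR on pain

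*Protocol article*

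**What the plan says.** Section 4.9 of the protocol article sets out the secondary analyses: "VAS pain at 24 h (ANCOVA adjusted for opioid dose), total opioid consumption (ANOVA or Kruskal–Wallis depending on distribution". The words that matter are "ANCOVA adjusted for opioid dose), total opioid consumption": the covariate for pain is the next outcome tested. A later sentence in the same section adds: "Postoperative pain analyses will additionally be adjusted for perioperative opioid consumption and surgery duration when appropriate".

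Other sections fix what kind of variable opioid use is:

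- **Timing.** Section 4.5 places randomisation on the day before surgery, after the baseline assessments. The later steps are "surgery → postoperative assessment within 24 h and analgesic assessment within 24–48 h postoperatively". The opioid variables listed in Section 4.8 are intraoperative and postoperative, so both follow randomisation.
- **Status.** Section 4.7.4: "Secondary outcomes include postoperative pain intensity assessed using the Visual Analogue Scale (VAS), postoperative analgesic use, patient satisfaction, and VR-related adverse effects". Section 3 sets the secondary VR comparisons "with respect to postoperative pain, analgesic use, and patient satisfaction".
- **Expected effect.** Section 1 cites studies in which patients who used anxiety-reduction methods had lower pain and needed fewer painkillers.
- **Window.** Section 4.7.4 has "postoperative analgesics measured from patient treatment charts within 24 and 48 h postoperatively". Table 2 puts "VAS pain, analgesic use" together in its row for the first 24 h after surgery. Section 4.5 gives 24–48 h.
- **Baseline pain.** Section 4.8 and Table 2 collect VAS before the VR session. It is not a covariate in the named pain ANCOVA, whereas the primary endpoint is adjusted for its own baseline.

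Section 4.9 also plans a linear mixed model over baseline, post-VR and postoperative times, with arm, time and their interaction. It does not name the measures to be modelled.

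**The concern.** A covariate is safe in a randomised comparison when treatment cannot have changed it. Opioid dose does not meet that condition. It is recorded after randomisation, the trial hypothesises that VR affects it, and patients in more pain plausibly receive more of it. Holding it fixed asks whether arms differ in pain among patients who took the same dose. Randomisation does not protect that comparison: it removes any part of the VR effect that shows up as a lower opioid requirement, and it mixes in the other reasons why patients receive a given dose.

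Postoperative pain is in the trial's hypothesis, in the objective given in the Abstract, and first in the list of secondary outcomes. If the adjusted model is reported as the effect of VR on pain, a real benefit could be understated, overstated, or suggested where net pain scores do not differ. No estimand or mediation aim is stated that would call for conditioning on dose.

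**Working it through.** The protocol states no figure for the 24 h pain endpoint, so there is none to reproduce. The check is of structure first, then of possible size. Every numerical input below is an assumption.

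**1. General identity (linear model).**
Adjusted effect = total effect − γ × (arm difference in opioid dose), where γ is the within-arm slope of VAS on dose. The two agree if the arms do not differ in dose or if γ = 0. The protocol does not give the sign of γ. It is positive if dose mainly tracks pain, and negative if dose varies mainly for other reasons and relieves pain strongly.

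**2. A simple model.**
- VR lowers latent pain by D.
- Dose rises by c per unit of latent pain, plus other variation. R² is the within-arm share of dose variance explained by latent pain.
- VAS equals latent pain minus b × dose, plus noise. The share of latent pain that opioid removes is k = b × c.

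Then:
- Total reduction in VAS = D(1 − k).
- Dose is lower under VR by cD.
- Within arm, latent pain has slope R²/c on dose, so γ = R²/c − b = (R² − k)/c.
- Adjusted reduction = D(1 − k) − (R² − k)D = D(1 − R²).

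The estimates coincide when R² = k. Adjustment shrinks the effect when R² > k and enlarges it when R² < k.

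**3. Numbers, with D = 10 mm assumed.**

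| R² | k | Total effect | Opioid-adjusted | Ratio |
|---|---|---|---|---|
| 0.50 | 0 | 10 × 1.0 = 10.0 mm | 10 × 0.50 = 5.0 mm | 0.50 |
| 0.50 | 0.20 | 10 × 0.8 = 8.0 mm | 5.0 mm | 0.63 |
| 0.25 | 0.40 | 10 × 0.6 = 6.0 mm | 10 × 0.75 = 7.5 mm | 1.25 |
| 0.10 | 0.40 | 6.0 mm | 10 × 0.90 = 9.0 mm | 1.50 |

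Simulation of this model with 4 million patients per setting gave the same values.

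**4. At the trial's arm size.** A separate simulation used two arms of 50, 4,000 replicates, and other assumed inputs, some with R² or k outside the range in step 3. Negative values favour VR.

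| Scenario | True total | Opioid-adjusted | Rejection: unadjusted → opioid-adjusted |
|---|---|---|---|
| A. Dose titrated to pain | −8 mm | −2.0 mm | 61% → 12% |
| B. Dose driven mainly by other factors, strong relief | −7 mm | −9.0 mm | 31% → 58% |
| C. VR lowers dose, net VAS unchanged | 0 | −1.4 mm | 5% → 10% |
| D. VR affects neither pain nor dose | 0 | 0.0 mm | 5% → 5% |

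With baseline VAS as the covariate and no opioid term, the mean estimates were −8.1, −7.0, 0.0 and 0.0 mm, matching the truth to within simulation error.

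**5. Precision from baseline VAS.** For an assumed correlation r between baseline and 24 h VAS, residual variance is multiplied by 1 − r²: 0.91, 0.75 and 0.64 for r = 0.3, 0.5 and 0.6, a saving of 9% to 36%.

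**The case against.** The strongest reply is that the problem is conditional and confined. If VR changes neither pain nor dose there is no bias, and when R² is close to k the distortion is small. The range of half to 1.5 times comes from the corners of an assumed grid. Opioid consumption is also tested between arms, so readers will see both outcomes, and the second adjustment sentence carries a qualifier. All of this stands, and it limits the severity. It does not repair the named ANCOVA, whose opioid covariate is unconditional, and the qualifier leaves the model to be chosen later.

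Four stronger readings are tempting, but the document does not support them.

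- **That intention-to-treat is broken.** It concerns analysing patients as randomised, which Section 4.9 keeps. The covariate changes what is estimated, not who is analysed.
- **That baseline VAS goes unused.** It is absent from this ANCOVA only. The mixed model's three times are exactly those at which Table 2 measures VAS, and Section 4.7.4 plans to compare preoperative with postoperative VAS. Leaving a baseline out of an ANCOVA under randomisation costs precision, not validity. The mixed model is only a partial safeguard, because its measures are unnamed and the general opioid-adjustment sentence could be read to cover it.
- **That the covariate includes drug given after the pain score.** Section 4.9 does not say which window its opioid dose uses. The differing windows make this possible, not established. Nor would a 0–24 h total settle it, since most sections place the pain score within 24 h rather than at 24 h.
- **That surgery duration is an equal problem.** It too is recorded after randomisation, but a VR effect on it is much less plausible.

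**Conclusion.** Wrong as written, and it should be fixed. The plan conditions its 24 h pain comparison on a post-randomisation variable that is also a secondary outcome and that the protocol expects VR to lower. If VR changes opioid use, or the pain that drives it, the adjusted arm difference can be too small or too large, and the direction cannot be known in advance. A reader might infer that the pain result is certain to be biased. The document does not support that, because the bias depends on an effect of VR that is hypothesised, not known.

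The size is illustrative only. It rests on a linear model with D = 10 mm, R² from 0.10 to 0.50 and k from 0 to 0.40, none of which is in the protocol. The primary STAI-S analysis and the intention-to-treat population are unaffected.

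**What to change.** In Section 4.9:

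1. Make the main model for 24 h VAS an ANCOVA on arm and baseline VAS, with neither opioid dose nor perioperative opioid consumption in it.
2. State that the opioid adjustment does not apply to the mixed model for VAS.
3. Analyse opioid consumption as its own endpoint over one stated window, the same in all arms, and reconcile Sections 4.5 and 4.7.4 and Table 2 with it.
4. If an opioid-adjusted pain model is kept, label it exploratory and not an estimate of the treatment effect.

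The cost is wording; baseline VAS is already collected. The wording should be settled before unblinding. The downside is that the main VAS result no longer speaks to pain at equal opioid dose, so the pain and opioid results must be reported and read side by side.

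### The secondary longitudinal mixed model does not adjust for baseline, so its group × time contrast is less precise than it could be, mainly for VAS pain

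*Protocol article*

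**What the plan says.** Section 4.9 handles baseline in two ways.

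- **Primary endpoint.** The change in STAI-S from baseline to just after the intervention "will be analyzed using one-way ANCOVA adjusted for baseline STAI-S".
- **Longitudinal analysis.** The response series is given as "Longitudinal measures (baseline → post-VR → postoperative") and "will be evaluated with a linear mixed-effects model including group, time, and group × time interaction". No baseline covariate is listed. The section adds: "Longitudinal analyses will primarily rely on linear mixed-effects models, which are robust to missing observations under missing-at-random assumptions".

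The mixed-model sentence does not name its outcomes. Section 4.7.4 points to two: "Preoperative and postoperative STAI-S and VAS will be compared for data analysis". Table 2 starts both series ("Day before surgery (pre-VR) Baseline STAI-S, VAS pain"). It then schedules VAS at all three times but STAI-S only before and after VR.

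Pain at 24 h also has its own ANCOVA in section 4.9. That model adjusts for opioid dose and, where appropriate, surgery duration. Baseline VAS is not named.

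**The concern.** If baseline is an outcome time and the group term is free, the model estimates a separate baseline mean for each arm. Section 4.5 puts baseline before randomisation, so the true baseline means are equal by design. Estimating three of them discards that information.

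Two consequences follow:

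- **VAS pain.** As written, the mixed model is the only named between-arm analysis that uses baseline pain, and it uses it inefficiently.
- **STAI-S.** If STAI-S enters the model, its baseline to post-VR contrast targets the same effect as the primary ANCOVA, but without adjustment. The two estimates can differ by chance, and the article does not say how they relate.

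**Working it through.** **Inputs.** The model terms and time points come from section 4.9. The article gives no correlation ρ between baseline and follow-up and no figure for the precision of this model, so there is no stated result to reproduce. I assume ρ = 0.3, 0.5 and 0.7, and the same SD σ at both times, with n patients per arm.

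**Step 1: what the contrast estimates.** With complete data and the listed terms, the group × time coefficient at post-VR is the difference between arms in mean change. This was checked by fitting a random-intercept model to three simulated three-arm, three-time data sets (42 per arm, ρ = 0.5):

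| Mixed-model group × time | Raw difference in change | ANCOVA | Chance baseline imbalance |
|---|---|---|---|
| −7.373 | −7.373 | −6.710 | 1.32 |
| −8.091 | −8.091 | −6.768 | 2.57 |
| −7.829 | −7.829 | −8.222 | −0.79 |

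The first two columns agree exactly. The gap to ANCOVA is about −(1 − ρ) × imbalance. In the first row, −0.5 × 1.32 = −0.66, against an observed −7.373 + 6.710 = −0.663.

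**Step 2: precision.** The variance of the between-arm contrast is:

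- follow-up only, ignoring baseline: 2σ²/n
- difference in change: (2σ²/n) × 2(1 − ρ)
- baseline-adjusted: (2σ²/n) × (1 − ρ²)

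The ratio of adjusted to change is (1 − ρ²) / [2(1 − ρ)] = (1 + ρ)/2. It depends on neither σ nor n, so it applies to VAS as well.

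| ρ | Change: 2(1 − ρ) | Adjusted: 1 − ρ² | Ratio (1 + ρ)/2 | Variance cut |
|---|---|---|---|---|
| 0.3 | 1.40 | 0.91 | 0.65 | 35% |
| 0.5 | 1.00 | 0.75 | 0.75 | 25% |
| 0.7 | 0.60 | 0.51 | 0.85 | 15% |

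A follow-up-only comparison scores 1.00 on this scale. The change contrast is therefore worse than ignoring baseline when 2(1 − ρ) > 1, that is, when ρ < 0.5. At ρ = 0.9 the cut shrinks to 5%.

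**Step 3: size of the STAI-S discrepancy.** The SD of the gap between the two estimates is about (1 − ρ)σ√(2/n). Section 4.3.1 gives 42 per arm and "a mean reduction of 8–10 points with a standard deviation of approximately 10 points", which may be the SD at one time or the SD of the reduction.

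- SD of 10 at one time: (1 − ρ) × 10 × √(2/42) = 1.53, 1.09 and 0.65 points at ρ = 0.3, 0.5 and 0.7.
- SD of 10 for change: σ = 10/√[2(1 − ρ)], so the gap SD is 10 × √[(1 − ρ)/2] × √(2/42) = 1.29, 1.09 and 0.85 points.

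**Step 4: validity.** In 20,000 simulated two-arm trials per setting (42 per arm, no true effect, two-sided 0.05), the change contrast rejected in 5.0%, 5.1% and 5.0% at the three correlations. ANCOVA rejected in 5.1%, 4.9% and 5.0%. Mean estimates were unbiased for both.

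**The case against.** The strongest reply is that no primary or named secondary endpoint rests on this model. STAI-S change has its baseline-adjusted ANCOVA, 24 h VAS has its own ANCOVA, and opioid use, satisfaction and rescue analgesia each have a named test. The statement about relying on mixed models is confined to longitudinal analyses and concerns missing data. Group, time and their interaction is a common and valid specification. All of this stands, and it is why the point is minor.

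A second reply is that the article never names group × time as the reported treatment effect, and the contrasts may be left to a fuller plan. That is fair, but it does not supply the adjustment. The other usual contrast from the same terms, the between-arm difference at a follow-up time, ignores baseline altogether when data are complete.

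A reader might infer that the trial loses power for its main hypothesis, by putting the 8-point difference and SD of 10 from section 4.3.1 into the change contrast. The documents do not support this. Those figures belong to the primary STAI-S comparison, which is tested by ANCOVA. For VAS the article gives neither a difference nor an SD, so only a proportional loss of precision can be shown.

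**Conclusion.** The point holds as a precision and consistency weakness in a secondary analysis. The planned model is unbiased with correct type I error. Baseline adjustment would cut the variance of its treatment contrast by 35%, 25% and 15% at correlations of 0.3, 0.5 and 0.7, and by little at high correlation.

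This rests on assumed correlations, equal SDs at the two times, and complete data. With missing values the contrast is no longer exactly the raw difference in change, but the baseline group effect stays free.

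The main effect is on VAS pain. For STAI-S a reader might infer that two competing primary results could arise. They would not: the ANCOVA is prespecified as primary, and a discrepancy of roughly 1 point (SD) in a supportive model does not displace it. Low severity.

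**What to change.** In section 4.9, replace the longitudinal model with one whose responses are the post-VR and postoperative values only. Its terms would be group, time, group × time, baseline, and baseline × time. Report the between-arm contrast at each post-baseline time. This treats baseline as the primary ANCOVA does.

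An equivalent alternative keeps baseline as a response but gives all arms a common baseline mean (time, plus group × post-baseline time). This needs baseline always to precede allocation. Section 4.5 states that order, on the day before surgery. Section 4.4 places allocation at a clinic visit, and section 4.8 places baseline on the day before surgery. These passages should be reconciled before this option is chosen; the covariate version is the safer default.

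The cost is one sentence, with no new data, visits or patients. A patient with no baseline value would drop out of the covariate model unless imputed, and section 4.9 already allows multiple imputation.
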